**Methods:**

A mixed methods study will be conducted, guided by the principles of sequential explanatory design. Quantitative results from a clinician survey will be followed by in-depth, semi structured interviews to explore findings in more depth through qualitative analysis. We will recruit from general and orthopaedic surgeons and registrars in a major tertiary hospital in a regional city in Australia (n ≈ 31). Data will be collected, independently coded and analysed using a qualitative descriptive approach. Quantitative and qualitative results will be merged during interpretation to provide complementary perspectives of interrelated contextual factors that influence health promotion activities amongst hospital surgeons.

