### Clinician survey

Surgeons will be invited to complete a short 17-item self-administered clinician survey to assess health behaviour risk factor management, perceived knowledge, confidence and attitudes towards preventative health (Additional file 1). The clinician survey asks respondents to report on proportions of clients seen over a recent period who they: (1) asked about smoking, nutrition, alcohol and physical activity; (2) assessed for readiness to change; (3) provided verbal and written advice on these risk factors and; (4) referred to other services for support in changing risk factors. These clinician practices are the dependent variables. The clinician survey also questions the participants about their knowledge and confidence in screening and managing each risk factor. In addition, attitudinal measures will be included for: (1) the clinicians’ opinion on the perceived effectiveness of the interventions; (2) the perceived importance of the intervention for the clients they see; (3) perceived work priority; and (4) perceived acceptability on the part of the client of raising the topic of lifestyle risk factors. The answers to these questions constitute the independent variables. All clinician survey items are measured on a 5-point Likert scale. The clinician survey has been adapted with permission from a previously developed instrument used to assess health behaviour risk factor management practices and capacity in community dwelling participants [18, 23].

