### Participants

The target participants for this study are general and orthopaedic surgeons, and their registrars who consult out of the elective outpatient clinic in a major tertiary hospital in a regional city in Australia. The clients presenting to this clinic are ambulatory, non-admitted clients. While this group may be seen as a representation of the general community-dwelling population, research indicates that patients presenting to hospital clinics are more likely to have higher rates of chronic disease than the general population [3, 4, 7].

As there are only a limited number of surgeons (general and orthopaedic) (*n* = 20) and registrars (*n* = 11) operating out of the study hospital, we will offer participation to all of these practitioners. Recruiting all surgeons and registrars consulting out of the hospital will increase the potential sample size, and provides a participant sample with differences in career stage and level of training. In qualitative description, the methodology seeks to gather enough data to saturate the explanation [27, 28]. Interviews will be continued until no interviewees are providing new information, and data saturation is determined [30]. If it is deemed that theoretical saturation is reached prior to full recruitment, then recruitment will discontinue [25, 27, 30].

We will recruit participants from one study site only. We have chosen to recruit participants from one study site only due to the heterogeneity that exists between hospitals in terms of infrastructure, clinical practice and resources, as well as broader contextual factors that may differ between areas serviced by hospitals such as the availability of, and access to, local preventative health providers and programs [31]. This study is part of a broader body of work, investigating health promotion in non-admitted secondary care patients. We have already undertaken a clinical trial investigating behaviour change interventions for non-admitted secondary patients in a single-hospital setting (ANZCTR trial id: ACTRN12616001331426). This proposed mixed-methods study aims to fill the gap in knowledge pertaining to surgeons’ actual involvement in the practice of health promotion in an ambulatory care setting; these results can be used in the design of subsequent clinical trials involving surgeons screening and recruiting secondary care patients for behaviour change interventions.

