### Recruitment

An email will be sent to all potential participants by their head of department, explaining the rationale for the study and the inherent requirements. The email will explain that participants can take part in the clinician survey, the interview, or both. The email will contain a link to the electronic version of the clinician survey. The email will also inform participants that a hard copy version of the clinician survey is available if this is preferred. The email will contain contact details for the research team for those individuals who would like more information. To assist with completion rates [32], two subsequent reminder emails with attached clinician survey link will be sent out through the same electronic channel, at four-weeks and eight-weeks post initial email.

Individual participants will be approached to discuss involvement in the interviews, and where interested, a time will be arranged with each clinician to undertake the interview. Every effort will be made to allocate sufficient time in the interview to discuss informed consent and undertake the interview. Participants will be given a Participant Information and Consent Form to complete prior to undertaking the interview. Where appropriate, and to coordinate scheduling, the coordination of the interview times may be facilitated through the personal assistants of the surgeons. To facilitate the development of interview topics and question design, we aim to have at least 5 clinician surveys completed and analysed before undertaking any interviews.

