### Analyses

#### Clinician survey

Consistent with published literature utilising this survey [18, 23], the relationship between the dependent variables (clinician practices) and independent variables (confidence, knowledge and attitudes) will be analysed. Due to the small sample of clinicians available for recruitment, dependant variables will be recorded as low, moderate or high. Low implementers will be defined as clinicians with screening and intervention scores, across all risk factors, in the first quartile. High implementers will be defined as clinicians with screening and intervention stores, across all risk factors in the fourth quartile. Given the relatively small sample size, a Generalized Estimating Equation will be used to estimate the parameters of a generalized linear model with a possible unknown correlation between outcomes [33]. The generalized estimating equation procedure extends the generalized linear model to allow for analysis of repeated measurements or other correlated observations [33]. Generalized estimating equations allows for the highlighting of moderators that do not directly correlate with the outcome of interest, but influence other related factors [33–35]. Analysis of the surveys will be used to offer exploratory themes, questions and question-related probes for the semi-structured interviews.

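### The small sample is given as the reason for using GEE, but at most 31 clinicians is a reason for caution with it: uncorrected robust intervals would tend to be too narrow

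*Protocol article*

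**What the plan says.** The Analyses section (Clinician survey) relates clinician practices to confidence, knowledge and attitudes, and introduces the model with: "Given the relatively small sample size, a Generalized Estimating Equation will be used to estimate the parameters of a generalized linear model". The rest of that sentence and the next one add a second reason: outcomes may be correlated, and GEE extends the generalised linear model to such data.

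The Participants section fixes the number available: "As there are only a limited number of surgeons (general and orthopaedic) (*n* = 20) and registrars (*n* = 11) operating out of the study hospital". It adds that "we will offer participation to all of these practitioners", so the whole eligible group at the single site is already invited. The survey is optional. Under Recruitment: "The email will explain that participants can take part in the clinician survey, the interview, or both".

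The Clinician survey section under Methods/design covers four risk factors; clinicians report the share of clients whom they "asked about smoking, nutrition, alcohol and physical activity". The analysis section recodes practices into three implementation levels and says that the survey results will supply exploratory material for the interviews.

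The article names no significance level, variance estimator, reference distribution or working correlation.

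**The concern.** The robust variance estimates the spread of the coefficients from the residuals of each cluster. Those residuals come from a model fitted to the same clusters, so they are too small on average. The shortfall matters little with many clusters and more with few. A small number of clinicians therefore calls for care with GEE; GEE does not cure it.

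A full analysis plan that took the printed reason at face value could treat the small-sample problem as solved and use default software output. Intervals for the association of knowledge, confidence and attitudes with practice would then be too narrow, and some chance associations would look real. In this sequential design the survey analysis feeds the interview questions, and the findings are meant to inform policy and later trials, so overstated associations could be carried forward.

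**Working it through.** **Number of clusters.** Participants section: 20 surgeons + 11 registrars = 31, which agrees with the n ≈ 31 in the Abstract. This needs every invited clinician to answer the survey. No response rate is given, so smaller numbers are shown as a range.

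**Direction, by hand.** Let B = Σ DᵢᵀVᵢ⁻¹Dᵢ and let rᵢ be the residuals of clinician i. The sandwich variance is B⁻¹(Σ DᵢᵀVᵢ⁻¹rᵢrᵢᵀVᵢ⁻¹Dᵢ)B⁻¹. The leverages Hᵢ = DᵢB⁻¹DᵢᵀVᵢ⁻¹ have traces that sum to the number of parameters q, so the average per clinician is q/N. For predictors measured once per clinician, the sandwich variance is too small by roughly a fraction q/N, and the standard error by roughly 1 − √(1 − q/N). With an intercept, q = predictors + 1:

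| Predictors | q | q/N, N = 31 | SE too small by | q/N, N = 20 | SE too small by |
|---|---|---|---|---|---|
| 1 | 2 | 0.065 | 3.3% | 0.10 | 5.1% |
| 3 | 4 | 0.129 | 6.7% | 0.20 | 10.6% |
| 6 | 7 | 0.226 | 12.0% | 0.35 | 19.4% |

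This is a rough guide. It ignores unequal leverage and the use of z in place of t.

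**Size, by simulation under no association.** All of the following are assumptions:
- two-sided 5% level;
- four outcomes per clinician (one per risk factor), with correlation 0.4;
- 1, 3 or 6 predictors, the same for the whole clinician or varying by risk factor;
- continuous outcomes, or binary outcomes with prevalence 0.5 or 0.25, in place of the three levels;
- independence working correlation (3,000 runs per setting) or exchangeable (800 runs).

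Rejection rate of the uncorrected robust z test, as the range over outcome types and predictor types:

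| Clinicians | 1 predictor | 3 predictors | 6 predictors |
|---|---|---|---|
| 31 | 5.5–8.2% | 7.2–9.4% | 7.1–11.8% |
| 20 | 7.1–10.1% | 7.4–11.9% | 9.5–16.7% |

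With 15 clinicians the range over 1 to 6 predictors is 8.3–22.0%, and with 10 it is 10.3–42.3%. A separate simulation gave about 7.5–12% at 31 and 9.5–18% at 20. Taken together: roughly 5.5–12% at 31 and 7–18% at 20.

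Relative to 5%, the multiple at 31 clinicians runs from 5.5/5 = 1.1 to 11.8/5 ≈ 2.4. Simulation error is about ±1 percentage point with 3,000 runs (1.96 × √(0.08 × 0.92/3000) ≈ 0.0097) and ±2 with 800, so the lowest figure, 5.5%, cannot be told apart from 5%.

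**After correction.** The Mancl-DeRouen variance replaces rᵢ by (I − Hᵢ)⁻¹rᵢ. It was used with a t reference on N − q degrees of freedom (29, 27 and 24 for 1, 3 and 6 predictors at N = 31). It rejects 2.4–4.4% at 31 clinicians, and 2.5–3.1% at 15 to 20 clinicians with 3 predictors. The separate simulation gave about 2–6%. A simpler degrees-of-freedom correction with a t reference rejects 3.7–6.6% at 31.

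**The case against.** The strongest reply is that the article never commits to an uncorrected sandwich variance, a z test or a 5% level. Such details are commonly left to a full analysis plan, which is not shown here. That stands. A reader might infer that the tests reject about twice as often as the plan claims; the documents do not support this, because no error rate is claimed and the multiple at 31 clinicians depends on the setting. A reader might also infer that the missing correction is itself an error, or that GEE cannot be used here. The first may be settled in the unseen plan, and the corrected results contradict the second.

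Secondly, the inflation depends on the model. Knowledge and confidence are asked for each risk factor, so predictors may vary within a clinician, and the inflation is then smaller. With continuous outcomes, within-clinician correlation 0.5 and 31 clinicians, such predictors gave 7.1–7.5% (one) and 7.9–8.1% (three), against 9.2% and 10.5% for predictors constant within a clinician. The definition of low and high implementers can also be read as one category per clinician, so four scores per clinician is an interpretation. Much higher rates would need models with far more predictors than the article proposes.

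Thirdly, the survey analysis is exploratory. The primary outcomes are to identify activities and explore attitudes, the interview script is revised as interviews proceed, and the limited number of participants is acknowledged. This lowers the severity.

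Finally, the article already gives a valid reason for GEE, correlated observations. That makes the repair easy, but the printed small-sample reason is still wrong.

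**Conclusion.** The point holds as an error of rationale with a practical consequence. Small sample size is not a reason to choose GEE, and the ceiling of 31 clinicians cannot be raised at this site. If the standard uncorrected variance and z reference were used, nominal 5% tests would reject roughly 5.5–12% of the time at full response and 7–18% with 20 responders, and more often with fewer. The direction is consistent; the size rests on the assumptions listed above. The consequence is overstated exploratory associations passed on to the interviews and the interpretation, not a failed confirmatory test. Severity: should be fixed.

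**What to change.** In the Analyses section (Clinician survey):

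- Delete the clause that gives sample size as the reason for GEE, and rest the choice on the correlation between outcomes of the same clinician.
- State that standard errors will use a bias-corrected sandwich variance, for example Mancl-DeRouen, with a t reference on clinicians minus parameters degrees of freedom.
- Report the associations as exploratory estimates with intervals.

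As a suggestion only, keep the number of predictors per model small, for example one composite each for knowledge, confidence and attitude.

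The cost is one or two sentences and a software option. Intervals become wider, the corrected test is somewhat conservative with many predictors (2.4% in one setting with 6 predictors and 31 clinicians), and fewer associations will reach significance.

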#### Interviews

Data from individual interviews will be collected and analysed promptly, to allow emerging themes to be added to and explored in following interviews. Qualitative description analysis requires the reading and re-reading of transcripts, allowing the development of a coding scheme that accurately reflects concepts in the text [25, 26]. Coding is a critical part of the data analysis stage and aims to merge concepts and themes that emanate from reviews of the interviews and corresponding text, taking the text from the descriptive to the interpretive [36]. The qualitative description process utilises open and axial coding of transcripts, which, in keeping with the concurrent methodological approach, will occur simultaneously [24]. Open coding describes the reading of interview transcription linearly with the aim of identifying concepts and then grouping concepts into categories and subcategories [36]. The analytic process may be used to identify the more general categories that these concepts are instances of, such as institutions, work activities, social relations and so forth [26]. Axial coding is the process of developing connections between code categories and sub-categories via a combination of inductive and deductive thinking [26]. Consistent themes are integrated, reducing the overall number of categories [26]. The emerging categories will be reviewed by the research team with the aim of using the categories to explain the factors that influence surgeons’ decisions to use health promotion activities.

Following open and axial coding, a process of selective coding is undertaken [37]. This process defines the central or core category, and its clear relationship to other categories [28, 37]. The core category has the analytic power to combine all categories to form an explanatory whole [28, 37]. Data will be coded and analysed independently by two investigators. The investigators will identify and code themes using NVivo 10.0 software (QSR International). An electronic codebook will be developed to assist with the coding scheme and data characterisation. The codebook will contain code definitions as well as rules related to each unique code. To improve reliability, a third investigator will review the codebook and samples of transcripts. Disagreement between investigators will be resolved through discussion, and where required, the thorough re-examining of transcripts. Categories will be represented visually using diagrams to illustrate the conceptual relationship between the emerging categories. See Table 1 for additional qualitative analysis details.

### Risk of Bias

This study seeks to avoid the weakness or intrinsic biases inherent in single method, single observer, and single theory studies by adopting a mixed methods approach [20]. It will involve a series of steps consistent with rigorous qualitative research [20, 21], including: note-taking during clinician interviews; systematic data coding and analysis; detailed documentation of analytic decisions to explicitly demonstrate the means of arriving at the codes, and to avoid overgeneralisation and speculative conclusions; including direct quotations from participants to offer readers some perspective on the evidence from which the study findings and conclusions are based; and reviewing data coding processes, analytic decisions, and resultant themes by the two investigators [38]. These steps allow for the triangulation of findings by the research team, with high degrees of team involvement required through the stages of data analysis and interpretation [28, 38]. This process is designed to increase rigor by decreasing the likelihood that substantial thematic ideas get overlooked, and ensure transparency in both data coordination and interpretation [28].

### Trial status

Further to the approval for the research from the ethics boards of the hospital and university, the study has also been approved by the Group Executive at the study hospital, including Executive Director of Acute Health and the Chief Medical Officer.

## Discussion

Hospitals play an important role in sick care, the provision of rehabilitation services, the promotion of health, and the prevention of disease [4]. These activities have been core components of hospital work; however, the increasing prevalence of lifestyle-related chronic diseases necessitates a more expanded scope, and standardised provision of initiatives to enable clients to take an active role in preventative health and chronic disease management [5, 7, 8]. This requires the reorientation of health care facilities to integrate health promotion, disease prevention and rehabilitation services in curative care [17]. Hospitals can have a strong influence on health behaviour, with patients demonstrating more responsiveness to health advice in situations when they are experiencing ill-health [39]. A fundamental necessity towards integrating health promotion in hospital settings is strong leadership at different levels of hospital governance [7, 8]. This leadership is epitomised by hospital surgeons, influential figures within both clinical settings, and by extension, hospital organisational culture and practice [16, 40]. Surgeons are seen as the predominant authoritative source of advice and expertise on health issues, having influential roles in both clinical and administrative structure [7, 10, 39]. In spite of this, information regarding the professional practice, and the opinions of these exemplars of clinical practice pertaining to preventative health are absent from the literature.

The primary outcomes of this study will be to: (1) identify what health promotion activities surgeons carry out in public hospitals, and (2) explore the attitudes of surgeons towards preventative health practice. The depth of insight gained from the study of these highly professionalised clinical groups will offer a distinctive perspective on current practice, as well as the challenges of implementing effective health promotion into surgical practice. The findings from this study will offer insight into individual, institutional and contextual factors that influence surgeons’ decisions to participate in health promotion activities.

There are a number of limitations to the proposed study design. A limited number of participants will be recruited for this mixed-methods study. The demographic characteristics of the surgeons who participate in this study will be captured to enable comparison to broader communities of surgeons. Additionally, participants will be recruited from one study site to minimise the range of external influences. Although this might limit the transferability of the findings to other hospital settings, to our knowledge this will be the first study to capture the opinions of hospital surgeons on this issue.

The findings from this research might be used to guide strategy and policy in both clinical and institutional levels around health promotion planning and practice. Gaining the insights from surgeons will be an important step towards the proposed reorientation of hospital practice towards more integrated health promotion settings, culminating in environments that permit patients to take active roles in preventative health and management.

## Abbreviations

ANZCTR: The Australian New Zealand Clinical Trials Registry
COREQ: Consolidated criteria for reporting qualitative research
